## Methods

### Settings

The study will take place within the administrative districts of Nepal (Jhapa administrative district) and Nigeria (Ibadan North, Ibadan North West, Ona Ara, and Akinyele local government areas). In each country, a minimum of 6 PHCs will be recruited for the study to represent a range of urban and rural settings.

Nepal is classified as a lower-middle-income country, with an estimated population of 28.1 million [19]. In a recent survey, 16.8% of individuals attending primary care facilities met the criteria for depression [20]. However, only 8.1% had sought care for their mental health [21]. Primary care facilities include PHCs, health posts, urban health centers, community health units, and primary

health care outreach clinics. In these facilities, services are delivered by medical officers, health assistants, staff nurses, auxiliary health workers, and auxiliary nurse midwives. However, medical officers and staff nurses are only available in PHCs [22]. The availability of mental health care in the country is limited to services largely provided through hospitals located in the larger cities [22]. The Jhapa administrative district has a total population of 812,650 people. Medical care is provided through 1 zonal hospital, 6 PHCs, 44 health posts, and 6 urban health centers [23]. Specialist outpatient mental health services are located in 2 private hospitals within the district. The mhGAP-IG was adopted by the government of Nepal and implemented in several districts after the major earthquake in 2015. The government has allocated a budget for district-level mental health care services to include the addition of 6 psychotropic drugs to those already freely available within health facilities and the strengthening of community mental health care services [24].

Nigeria is classified as a lower-middle-income country. It is home to the largest national population in Africa (195.9 million as of 2018) [25]. Recent research in the country estimated a 5.5% prevalence of depression [26]. However, similar to other LMICs, 85% of individuals living with a mental disorder receive no treatment [27]. Ibadan metropolis has 11 local government areas and a population of approximately 3.5 million people. The mental health services in Ibadan are primarily provided by 2 large general hospitals. There are 186 PHCs, each serving a population of approximately 10,000 people. The study will be conducted in 2 urban and 2 rural local government areas. PHCs in Nigeria are staffed by nonphysician health workers (nurses, community health officers, and community health extension workers) who provide treatment for common disorders (including depression) presenting in primary care. The country adopted the mhGAP-IG as a national program for expanding mental health services in 2013, and PHCs are among those where providers have received training in the use of the mhGAP-IG. In Ibadan, PCWs are provided with unstructured supervision by a supervisory general practitioner who typically oversees a group of 6-8 PHCs within a local government area.

The use of digital technology in both Nepal and Nigeria has seen exponential growth in recent years, with the trend expected to continue. In Nepal, mobile penetration was 133% in 2018, which is greater than 100% because most Nepalis have multiple mobile phone provider contracts [28]. In the same year, mobile penetration was estimated to be 49% in Nigeria, with a projected increase to 55% by 2025 [29]. A total of 36% of mobile phone connections in Nigeria are linked to a smartphone.

## Technology

A 2015 WHO consultation on the 5-year impact of the mhGAP-IG v1.0 highlighted the demand for an e-version. Respondents identified increased utility and coverage of an electronic guide as reasons for its development. An e-version also creates new opportunities for quality improvement (eg, in remote supervision). A year later, a privately developed e-version of the mhGAP-IG for use in Afghanistan was used for 3000 screenings and 600 referrals [30]. Community health workers reported good acceptability of the mobile app. An e-version of the mhGAP-IG v2.0 was launched by the WHO in October 2017 for Apple and Android smartphones and tablets.

The Emilia project comprises 3 phases: (1) development of an adapted e-mhGAP-IG, (2) feasibility testing, and (3) knowledge transfer and future work. In phase 1, an updated version of the WHO's electronic intervention guide was developed using a human-centered design approach. Human-

centered design is an approach that actively engages stakeholders in the design process using cutting-edge methods to ensure that interventions are optimized for both front-line use and local and national implementation [31]. The approach includes qualitative research with key stakeholders to identify motivations, an iterative process of intervention development and prototyping, and intervention evaluation. The updating of the e-mhGAP-IG included individual and group interviews with PCWs in Nepal and Nigeria to understand the accessibility of technology by health workers, their use patterns, and their preferences for the design of the e-mhGAP-IG. The findings showed that most health workers had access to a personal smartphone, were familiar with the use of various smartphone apps, and valued the idea of an e-version of the mhGAP-IG. Requested features included decision support functions, ability to be used in offline mode, and an easy-to-use design that limited text entry. The formative work also highlighted the importance of recording patient information for review and use in supervision through a clinical dashboard. The resulting updated app features a *reference mode* for training and exploration and a *patient mode* for completing an assessment or management visit with an individual. Health workers can access a brief description of possible conditions through the *Master Chart* (a feature of mhGAP-IG 2.0) and then select modules for further assessment. The mhGAP-IG algorithms are presented in a single-page series of yes or no questions with a *proceed* button, indicating when the end of an algorithm has been reached. Health workers are then presented with an assessment summary, including any additional information to consider, such as whether the individual belongs to a *special population* that may affect treatment decisions. Within the app, health workers can complete additional information for a patient's record, including measures of severity, functioning, and information for follow-up visits. All information is accessible in a clinical dashboard that summarizes key information for each visit as well as aggregate information to help supervisors identify any issues that can be addressed in supervision (eg, overmedication or inaccurate diagnosis). The e-mhGAP-IG will be available in both English and Nepali. Prototypes of the app have been tested with health workers in Nepal (5 iterations) and Nigeria (4 iterations) who found the app to have an intuitive design that is appropriate and feasible for use in clinical work.

### Study Design

A feasibility cluster randomized controlled trial (cRCT) will be conducted to evaluate and compare the implementation outcomes [32] and clinical outcomes of the adapted e-mhGAP-IG v2.0 and the paper version of the mhGAP-IG v2.0. A total of 10 PHCs in each country (Nepal and Nigeria) will be randomized to training, supervision, and care delivery using the paper mhGAP-IG (control arm) or the e-mhGAP-IG (experimental arm), and outcomes of PCWs and patients will be collected over a 9-month period (Figure 1). Data collected through the feasibility study will be used to further refine the intervention (eg, acceptability and feasibility for randomization and recruitment) and power a subsequent cRCT.

Figure 1.

[figure not shown]

Feasibility study patient and provider data collection procedure. mhGAP: Mental Health Gap Action Programme;  $P_0$ : patient pre training assessment;  $P_1$ : patient baseline health care appointment assessment;  $P_2$ : patient 3 months post baseline health care appointment; PCW: primary care worker;  $PCW_0$ : primary care worker baseline assessment;  $PCW_1$ : primary care worker immediate post training assessment;  $PCW_2$ : primary care worker 3 months post training assessment;  $PCW_3$ : primary care worker 8 months post training assessment;  $S_0$ : Supervisor baseline assessment;  $S_1$ : Supervisor 8 months post training assessment.

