**Methods**

A feasibility cRCT will be conducted in Nepal and Nigeria to evaluate the feasibility of the e-mhGAP-IG for use in depression diagnosis and treatment. In each country, an estimated 20 primary health clinics (PHCs) in Nepal and 6 PHCs in Nigeria will be randomized to have their staff trained in e-mhGAP-IG or the paper version of mhGAP-IG v2.0. The PHC will be the unit of clustering. All PCWs within a facility will receive the same training (e-mhGAP-IG vs paper mhGAP-IG). Approximately 2-5 PCWs, depending on staffing, will be recruited per clinic (estimated 20 health workers per arm in Nepal and 15 per arm in Nigeria). The primary outcomes of interest will be the feasibility and acceptability of training, supervision, and care delivery using the e-mhGAP-IG. Secondary implementation outcomes include the adoption of the e-mhGAP-IG and feasibility of trial procedures. The secondary intervention outcome—and the primary outcome for a subsequent fully powered trial—will be the accurate identification of depression by PCWs. Detection rates before and after training will be compared in each arm.

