## Participants

An estimated 20 PHCs in Nepal and 6 PHCs in Nigeria will be identified by local partners. Clinic managers and PCWs will be approached by local research staff with invitations to participate in the study. On the basis of the staffing of PHCs, we estimate that 2-5 PCWs per PHC will participate, equivalent to 40 PCWs in Nepal and 30 PCWs in Nigeria, approximately 15-20 health workers per arm per country (Figure 2).

Figure 2.

[figure not shown]

Emilia (E-mhGAP Intervention Guide in Low- and Middle-Income Countries: Proof-of-Concept for Impact and Acceptability) flow chart. e-mhGAP-IG: electronic Mental Health Gap Action Programme Intervention Guide; mhGAP-IG: Mental Health Gap Action Programme Intervention Guide.

PCWs will be eligible to participate if they are employed by the PHC or government and have roles and responsibilities related to the use of the mhGAP-IG (eg, direct clinical use or supervision). All relevant PCWs, regardless of individual study participation, will receive training in the mhGAP-IG v2.0 (electronic or paper version) and have ongoing remote support and supervision by health care providers with enhanced mental health knowledge.

Patients presenting to primary care will be enrolled in the study to evaluate their perceptions of services and to obtain descriptive information on detection rates and treatment impact to inform a

subsequent fully powered cRCT. There will be 2 periods of patient enrollment: *pre training*, which is before PCWs receive mhGAP-IG training, and *post training*, which is after PCWs have received mhGAP-IG training. For the 1-month before the mhGAP-IG training, a random selection of adults presenting to primary care will be screened by research assistants to determine depression status, which will be compared with documented diagnoses by the PCWs. Similarly, beginning at 3 months post training, a random selection of patients will be screened by research assistants for depression status. This posttraining patient enrollment will last a minimum of 3 months.

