## Randomization and Allocation Concealment

Clinics will be randomized to the control or intervention conditions, with equal number of clinics in either group (1:1). Randomization will be carried out independently (to ensure concealment) by the trial statistician via a computer-generated random sequence before participants are recruited or the intervention is initiated. PCW selection will be performed according to health staffing levels before randomization of clinics to a study arm. Blinding or masking of participants, clinicians, and fieldworkers will not be possible, as it will be clear which conditions clinics or municipalities are assigned to during implementation and data collection. However, the senior and junior trial statisticians who carry out the randomization will not know the characteristics of the clinics being randomized, and the primary statistical analysis will also be blinded to allocation status.

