## Statistical Power and Sample Size Calculation

The study will take place in 1 government administrative region in Nepal and 4 in Nigeria. We will identify approximately 20 PHCs in Nepal and 6 in Nigeria. In each country, half of the PHCs will be randomly allocated to either the e-version or the paper version of the mhGAP-IG. As the clinics vary in size, we will assess at least two staff members in each clinic, with an estimated 2-5 health workers per facility and an overall enrollment of 40 PCWs in Nepal and 30 PCWs in Nigeria. Regarding patient numbers, on the basis of the sample size for the study by Sangha et al [34] on smartphone app for improving cognition to improve case detection, we will conduct within-arm comparison detection rates if at least 40 patients screen positive on the Patient Health Questionnaire (PHQ-9) in the research assistant interview in the 1-month pretraining period and in the first month of the posttraining patient enrollment period, which begins after 3 months of intensive supervision. This will allow us to detect a within-arm increase in the clinical case identification rate of 43% for the e-mhGAP-IG after the implementation of the e-version with 90% power at the 5% level of significance, assuming an intraclass correlation coefficient of 0.02. For example, with a 10% detection rate pretraining, 2 patients would receive a health worker depression diagnosis out of 20 patients screening positive. After training, the detection rate would increase to 53%, which equates to 11 patients diagnosed by a health worker out of 20 patients screening positive.

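### The protocol gives two conflicting counts of randomised clinics (10 per country, or about 20 in Nepal and 6 in Nigeria), and neither Nepal count fits the 6 PHCs listed for the only Nepal district

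*Protocol*

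**What the plan says.** Four places in the protocol give a number of clinics.

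- Study Design: "A total of 10 PHCs in each country (Nepal and Nigeria) will be randomized to training, supervision, and care delivery". There is no qualifier.
- Abstract, Methods: "an estimated 20 primary health clinics (PHCs) in Nepal and 6 PHCs in Nigeria will be randomized".
- Participants: "An estimated 20 PHCs in Nepal and 6 PHCs in Nigeria will be identified by local partners".
- Statistical Power and Sample Size Calculation: "We will identify approximately 20 PHCs in Nepal and 6 in Nigeria". Half of the clinics in each country then go to each arm.

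Settings adds only a floor: "In each country, a minimum of 6 PHCs will be recruited for the study". For Jhapa, the single Nepal district, the same section says "Medical care is provided through 1 zonal hospital, 6 PHCs, 44 health posts, and 6 urban health centers", and notes that "medical officers and staff nurses are only available in PHCs".

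Randomization and Allocation Concealment describes a computer-generated sequence with equal numbers of clinics per arm. The statisticians who run it "will not know the characteristics of the clinics being randomized". The section names no stratum or other balancing factor.

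**The concern.** The clinic is the unit of randomisation, so the number of clinics is the basic sample size of the trial. It sets the degrees of freedom for any cluster-level comparison, the patients per cluster and hence the design effect. It also limits what the study can say about between-clinic variation when its data are used to power the later trial. A reader cannot tell whether Nepal contributes 10 or 20 clusters, or Nigeria 10 or 6.

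In Nepal the protocol also leaves open what a cluster is. Used as a facility category, PHC covers only 6 sites in Jhapa, so other facilities must be included. Their staffing differs, and the outcome of interest is a diagnosis made by those staff. The mix of facility types in each arm therefore matters, and nothing in the text says it will be balanced.

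**Working it through.** **1. Counts side by side (1:1 within country).**

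| Source | Nepal | Nigeria | Total | Per arm |
|---|---|---|---|---|
| Study Design | 10 | 10 | 20 | 5 v 5 in each country |
| Abstract, Participants, sample size section | 20 | 6 | 26 | 10 v 10 and 3 v 3 |
| Settings | at least 6 | at least 6 | – | not fixed |

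The Settings floor is compatible with both versions and settles nothing.

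**2. Do the health worker totals settle it?** The protocol expects 40 workers in Nepal, 30 in Nigeria and 2 to 5 per clinic. Nepal: 40/20 = 2 or 40/10 = 4. Nigeria: 30/6 = 5 or 30/10 = 3. All four values lie within 2 to 5, so they do not discriminate.

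**3. Facilities in Jhapa.** There are 6 PHCs. With 10 clusters, at least 10 − 6 = 4 are other types; with 20, at least 20 − 6 = 14. Including health posts and urban health centers, 6 + 44 + 6 = 56 facilities exist, so either count is reachable once those types are declared eligible.

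**4. The plan's own power figure.** The sample size section claims 90% power at the 5% level for a within-arm rise from 10% to 53%, with an ICC of 0.02 and a worked example of 20 screen-positive patients per period. It states neither the clusters per arm nor whether the test is one- or two-sided. Taking one arm in one country, with k clinics:

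- m = 20/k, DEFF = 1 + (m − 1) × 0.02, effective n = 20/DEFF
- power = Φ{[0.43 − z√(2 × 0.315 × 0.685/n)] / √[(0.10 × 0.90 + 0.53 × 0.47)/n]}, with n the effective n and z = 1.96 (two-sided) or 1.645 (one-sided)

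| Clinics per arm | m | DEFF | Two-sided power | One-sided power |
|---|---|---|---|---|
| 3 | 6.67 | 1.113 | 82% | 90% |
| 5 | 4 | 1.06 | 84% | 91% |
| 10 | 2 | 1.02 | 86% | 92% |

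The stated 90% is reproduced to within about 2 points on a one-sided reading. With 40 per period, two-sided power is 98% to 99%. The choice of count moves the two-sided figure by about 4 points at most.

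**5. Where the count matters more.** A cluster-level comparison between arms within a country has 2k − 2 degrees of freedom: 8 for 5 v 5 (t = 2.31), 18 for 10 v 10 (t = 2.10) and 4 for 3 v 3 (t = 2.78). The protocol expects 200 screened patients per arm per country per month, or 40, 20 or 67 per clinic respectively. Applying the ICC of 0.02 to all screened patients (an assumption), the monthly design effect is 1 + 39 × 0.02 = 1.78, 1 + 19 × 0.02 = 1.38 or 1 + 65.7 × 0.02 = 2.31.

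**6. Facility-type balance in Nepal.** Assume all 6 PHCs are among the clusters and the only restriction is equal numbers per arm. With 20 clusters, P(x PHCs in one arm) = C(6,x) × C(14,10−x)/C(20,10). This gives 0.0054 for x = 0 and 0.0650 for x = 1. A 5-1 or worse split has probability 2 × (0.0054 + 0.0650) = 14%; an even 3-3 split has probability 37%. With 10 clusters, P(x) = C(6,x) × C(4,5−x)/C(10,5), and the figures are 2 × 0.0238 = 5% and 48%.

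**The case against.** **The counts are only estimates.** Three of the four places say estimated or approximately, and two speak of identifying clinics rather than randomising them. This does not reconcile them. The abstract says that 20 and 6 will be randomised. Nepal differs by a factor of two, while Nigeria differs in the opposite direction: 10 clinics cannot be randomised from 6 identified.

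**PHC may be a generic term.** The protocol expands it as primary health clinic, and in Settings also uses it for one Nepali facility category. That may well explain the Jhapa mismatch, and it stands as an explanation. The eligible types still need naming, because Settings itself separates the categories and says their staffing differs. It restricts only two cadres to PHCs, so it does not show that facility type alone decides who diagnoses.

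**A reader might infer that allocation is unstratified and arm balance is left open.** The text does not support that. Equal clinic numbers per arm are fixed, and so is a half-and-half split within each country. The protocol nowhere says unstratified; it is silent on strata, and masking the statisticians to clinic characteristics does not exclude coded strata. Only balance by facility type and by urban or rural setting is unaddressed.

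**A reader might also infer that imbalance would be inseparable from the arm effect.** In Nepal it would not be. With 20 clusters, even a 6-0 split leaves 4 other facilities in one arm and 10 in the other, so the two are never fully collinear, although adjustment would be weak. The sample size calculation concerns a within-arm change, which facility mix does not confound if the same clinics supply both periods.

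**Conclusion.** The contradiction in the number of randomised clusters is certain and rests on no assumption: 20 in total by one section, 26 by three others, with Nepal at 10 or 20 and Nigeria at 10 or 6. It is equally certain that at least 4 of 10 or 14 of 20 Nepal clusters fall outside the PHC category as Settings uses it, and that the protocol does not name the other types as eligible.

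The consequence for the stated within-arm power is modest, about 4 points two-sided. It is larger for between-arm description and for planning the full trial, where degrees of freedom per country range from 4 to 18.

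The balance point is secondary and conditional. The 14% chance of a 5-1 or worse split assumes 20 Nepal clusters, all 6 PHCs included and no restriction beyond 1:1. It shows what an unnamed stratum could cost; it does not show that strata are absent.

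**What to change.** 1. Give one clinic count per country in the abstract, Settings, Study Design, Participants and the sample size section. The simplest edit is to bring Study Design into line with 20 and 6, which three places including the sample size section give. If a different number was in fact randomised, state that number everywhere.
2. In the sample size section, state the clusters per arm, the patients per cluster and the sidedness behind the 90%.
3. Name the Nepal facility types that count as clusters, and use PHC in one sense only.
4. State whether allocation is balanced on facility type in Nepal and on setting in Nigeria. The half-and-half split within country is already there and needs no change.

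If randomisation has not happened, balance on facility type using coded labels, so that the statisticians stay masked, and keep equal clinic numbers per arm overall. Six PHCs and 14 others split evenly as 3-3 and 7-7. In Nigeria, 3 urban and 3 rural clinics (an assumed mix) could not each be split 1:1, so separate stratum lists could give 4 v 2 overall; the overall constraint must take precedence.

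The protocol's Results section says data collection began in January 2021, and randomisation was to precede recruitment, so allocation is probably done. In that case, report balance by facility type, adjust between-arm descriptions for it where the number of clusters allows, and carry the stratification to the full trial.

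The cost is a few sentences and one baseline table row, or a coded list if allocation is still open.

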## Participants

An estimated 20 PHCs in Nepal and 6 PHCs in Nigeria will be identified by local partners. Clinic managers and PCWs will be approached by local research staff with invitations to participate in the study. On the basis of the staffing of PHCs, we estimate that 2-5 PCWs per PHC will participate, equivalent to 40 PCWs in Nepal and 30 PCWs in Nigeria, approximately 15-20 health workers per arm per country (Figure 2).

Figure 2.

[figure not shown]

Emilia (E-mhGAP Intervention Guide in Low- and Middle-Income Countries: Proof-of-Concept for Impact and Acceptability) flow chart. e-mhGAP-IG: electronic Mental Health Gap Action Programme Intervention Guide; mhGAP-IG: Mental Health Gap Action Programme Intervention Guide.

PCWs will be eligible to participate if they are employed by the PHC or government and have roles and responsibilities related to the use of the mhGAP-IG (eg, direct clinical use or supervision). All relevant PCWs, regardless of individual study participation, will receive training in the mhGAP-IG v2.0 (electronic or paper version) and have ongoing remote support and supervision by health care providers with enhanced mental health knowledge.

Patients presenting to primary care will be enrolled in the study to evaluate their perceptions of services and to obtain descriptive information on detection rates and treatment impact to inform a

subsequent fully powered cRCT. There will be 2 periods of patient enrollment: *pre training*, which is before PCWs receive mhGAP-IG training, and *post training*, which is after PCWs have received mhGAP-IG training. For the 1-month before the mhGAP-IG training, a random selection of adults presenting to primary care will be screened by research assistants to determine depression status, which will be compared with documented diagnoses by the PCWs. Similarly, beginning at 3 months post training, a random selection of patients will be screened by research assistants for depression status. This posttraining patient enrollment will last a minimum of 3 months.

On the basis of prior data on primary care service use and screening depression rates, we anticipate being able to screen approximately 50% of adult patients presenting to primary care, with a possibility of screening a higher percentage depending on patient flow in the facility [33]. Therefore, we anticipate screening approximately 200 patients per arm per country per month (ie, 400 patients per country in the 1-month pretraining patient enrollment period and 1200 patients per country in the 3-month posttraining patient enrollment period).

Inclusion criteria for patients to be screened include the following:

- Attending PHC for treatment of a new case at recruitment
- Reached the age of adulthood (ie,  $\geq 18$  years)
- Fluent in Nepali (Nepal only) or English or Yoruba (Nigeria only).

Adult attendees will be deemed ineligible for the study if they are unable to understand or complete study assessment (eg, individuals with severe learning disability or dementia), unable to provide informed consent, or have a medical emergency requiring immediate intervention.

All patients who meet the eligibility criteria and choose to enroll in the study will then be screened by a research assistant to determine their depression status. Following this screening, patients will be evaluated by a PCW who will make an independent diagnosis without speaking to the research assistant or reviewing the screening results. Administration of screening tools may occur before or after the patient meets the health worker based on the workflow of the clinics. After patients meet the PCWs, a research assistant will review the provider's case notes to document whether or not a depression diagnosis was made.

